### Sample size

2.5

This study is designed as a phase II randomized, non-comparative trial, with pCR as the primary endpoint. According to Amaria et al. (21), a 60% pCR rate may be assumed in arms A and B. A sample size of 27 patients in each arm is sufficient to give at least a 90% probability of rejecting a 30% pCR rate with an exact 5% one-sided significance test when the true pCR rate is 60%. The null hypothesis of a pCR of 30% will be rejected if a pCR is observed in at least 12 patients.

According to Huang et al. (25), a pCR rate of about 30% may be assumed in arm C. A sample size of 34 patients is sufficient to give an 80% probability of rejecting a pCR rate of 15% with an exact 5% one-sided significance test when the true pCR rate is 35%. The null hypothesis of a pCR of 10% will be rejected if a pCR is observed in at least 10 patients.

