### Data analysis

2.6

All enrolled patients receiving at least one dose of the study medication will be considered the intention-to-treat population (ITT). The patient subgroup of the ITT population receiving at least one dose of the study drug will define the safety population. The analysis of efficacy endpoints will be performed in the ITT population, whereas the safety analysis will be performed in the safety population. A primary data analysis assessing the primary endpoint will be available after the neoadjuvant phase. A final data analysis will be available at study closure. The safety analysis will be completed within 12 months from the last visit of the last patient.

Primary endpoint results will be reported as counts and rates with confidence intervals. No comparisons among arms are planned. Demographical and clinical characteristics will be presented as descriptive statistics and summarized according to the treatment arm. Categorical variables will be given as counts and percentages, quantitative ones as mean and standard deviation, or median and interquartile range, as appropriate. No adjustment for multiple testing will be made.

Safety and tolerability will be assessed regarding AEs, laboratory data, ECG data, vital signs, and weight, which will be collected for all patients. AEs [both in terms of MedDRA preferred terms (26) and CTCAE 5.0 grade (27)], laboratory data, ECG data, vital signs data, and weight will be listed individually by the patient and summarized. Prevalence of related AEs, by grade, will be presented with a 95% CI. Survival will be represented with Kaplan-Meier curves, from which the median with 95% CIs will be derived.

Due to the small sample size, statistical analysis of biomarkers data will be conducted with the aim of hypothesis generation. A complete description of the data will be done. For biomarkers that might change over time due to treatment, levels before and after treatment will be compared with appropriate statistical tests based on the data type. Correlation with outcomes will be evaluated with univariate regression models. p ≤ 0.05 will be considered significant, and no adjustment is planned for multiple comparisons due to the exploratory nature of the analysis.

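### Section 2.5 fixes the primary decision as a bare pCR count whatever number is analysed; in arm C, one to three undosed patients would take power below the stated 80%, which an exact test at the attained n would avoid

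*Protocol article*

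**What the plan says.** Section 2.5 (Sample size) describes each arm's decision twice, once as a test and once as a count.

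- **Arms A and B.** The design claim is "A sample size of 27 patients in each arm is sufficient to give at least a 90% probability of rejecting a 30% pCR rate", and the method is an exact one-sided 5% test at a true rate of 60%. The rule that follows is "The null hypothesis of a pCR of 30% will be rejected if a pCR is observed in at least 12 patients".
- **Arm C.** The design claim is "A sample size of 34 patients is sufficient to give an 80% probability of rejecting a pCR rate of 15"%, again with an exact one-sided 5% test, at a true rate of 35%. The rule that follows is "The null hypothesis of a pCR of 10% will be rejected if a pCR is observed in at least 10 patients".

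Section 2.2 (Selection of subjects) sets enrolment at 88.

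Section 2.6 (Data analysis) defines the efficacy population by dosing: "All enrolled patients receiving at least one dose of the study medication will be considered the intention-to-treat population (ITT"). For the primary endpoint it adds "Primary endpoint results will be reported as counts and rates with confidence intervals". It does not mention the test or the counts again.

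**The concern.** An exact binomial cut-off belongs to a particular number of patients and moves in steps as that number changes. Section 2.5 prints the cut-off without that condition, while section 2.6 makes the number analysed an outcome of the trial: each patient who is enrolled but never dosed leaves the set. Because 27 + 27 + 34 = 88, nobody is enrolled to cover such losses.

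If an arm's analysed number differs from plan, the two descriptions in section 2.5 can disagree. The exact 5% test may reject where the printed count does not, or the reverse. At stake are the stated power in arm C and, with a surplus, the stated 5% level in arms A and B. The trial is open-label, so which description governs should be settled before responses are known.

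**Working it through.** **Inputs (section 2.5).** Arms A and B: n = 27, null 30%, true rate 60%, count 12, stated power at least 90%. Arm C: n = 34, null 15%, true rate 35%, count 10, stated power 80%. All arms: exact, one-sided, 5%.

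**Assumption.** The document gives no number of undosed or surplus patients. A departure of one to three per arm is assumed.

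**Formulas.** For X ~ Binomial(n, p) and a count r:

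- size = P(X ≥ r | null rate)
- power = P(X ≥ r | true rate)
- exact cut-off at n = the smallest r with P(X ≥ r | null rate) ≤ 0.05

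**Step 1: reproduce the plan, arm C.** With n = 34 and r = 10, size is 2.40% and power 80.4%, so the stated 80% is reproduced with 0.4 points to spare. The rule sentence names a null of 10%, but under 10% the size of this rule would be 0.14% and the exact cut-off would be 7. The count of 10 therefore belongs to the 15% null, which is used below. The conflict between the two nulls is a separate matter.

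**Step 2: arm C at other sizes.**

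| n analysed | Count 10: size | Count 10: power | Exact cut-off | Its size | Its power |
|---|---|---|---|---|---|
| 31 | 1.24% | 68.9% | 9 | 3.41% | 81.1% |
| 32 | 1.56% | 73.2% | 9 | 4.13% | 84.2% |
| 33 | 1.95% | 77.0% | 9 | 4.95% | 86.8% |
| 34 | 2.40% | 80.4% | 10 | 2.40% | 80.4% |
| 35 | 2.92% | 83.5% | 10 | 2.92% | 83.5% |
| 38 | 4.95% | 90.4% | 10 | 4.95% | 90.4% |
| 39 | 5.79% | 92.1% | 11 | 2.50% | 85.5% |

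The power given up by holding the count at 10 is:

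- n = 33: 86.8 − 77.0 = 9.8 points
- n = 32: 84.2 − 73.2 = 11.0 points
- n = 31: 81.1 − 68.9 = 12.2 points

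At 9 responders out of 33 the stated exact test rejects and the printed rule does not. From n = 34 to n = 38 the count of 10 meets both targets.

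**Step 3: arms A and B.** At n = 27 the printed 12 gives size 7.98% and power 96.6%, so the 5% level is already missed at the planned number. The exact cut-off there is 13 (size 3.59%, power 92.6%).

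| n analysed | Count 12: size | Count 13: size | Count 13: power | Exact cut-off |
|---|---|---|---|---|
| 25 | 4.42% | 1.75% | 84.6% | 12 (power 92.2%) |
| 26 | 6.03% | 2.55% | 89.2% | 13 |
| 27 | 7.98% | 3.59% | 92.6% | 13 |
| 28 | 10.28% | 4.91% | 95.0% | 13 |
| 29 | 12.94% | 6.52% | 96.7% | 14 (power 92.9%) |

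Replacing 12 by 13 would repair the planned case but not the dependence on n. A fixed 13 exceeds 5% at n = 29, and at n = 25 it loses 92.2 − 84.6 = 7.6 points of power. Between n = 26 and n = 28 recalculation changes nothing.

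**The case against.** The strongest reply is that section 2.5 already names the method, the level and the null. On that view the counts only illustrate the test at the planned size, and the handling of a different size belongs in the full protocol or analysis plan, which an article need not repeat. This carries weight: the named test can be recomputed at any n, and the article's silence on replacing undosed patients is no finding. But section 2.5 does more than stay silent. It says the null will be rejected at a stated count, so recomputing would depart from the rule as printed.

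Second, the trigger is assumed. Nothing in the article points to over-enrolment, and one dose is enough to stay in the analysis, so patients who are dosed but never reach surgery do not reduce n. This stands, and it limits the exposure to patients never dosed.

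Third, the arm C harm is in the conservative direction: size falls to 1.95% at n = 33, and power drops by only 80.4 − 77.0 = 3.4 points from plan. The large gain from a cut-off of 9 partly reflects the discreteness of the test. That is correct, but power is still below the stated 80% and the remedy needs no extra patients.

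A reader might go further and infer that each count is valid only at exactly 27 or 34 patients, so that one patient more or fewer breaks the design in every arm. The figures do not support this. The count of 10 holds from 34 to 38. The count of 12 is not valid at 27 in the first place, so one patient more worsens an existing error. A reader might also infer that a 95% interval would contradict the test, since at 13/27 the Clopper-Pearson interval is 28.7% to 68.1% and contains 30%. Section 2.6 does not use an interval to decide, so this is no contradiction.

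**Conclusion.** The concern holds in a limited form. Section 2.5 fixes the decision by a count that ignores the number analysed, while section 2.6 lets that number vary and enrolment has no margin.

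The clearest consequence is in arm C. If one to three patients go undosed, the printed rule has power of 77.0% down to 68.9%, whereas the exact test the plan names would keep it between 81.1% and 86.8%. The type I error in arm C is not at risk unless at least 39 patients are analysed.

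In arms A and B the excess over 5% at the planned size is a separate error. The point here is only that a fixed count, even the exact 13, would exceed 5% from n = 29, and that the printed 12 reaches 10.3% at n = 28.

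These conclusions rest on the 15% null and 35% true rate for arm C, the 30% and 60% rates for arms A and B, and the assumed departure of one to three patients per arm. The change is worth making because it is cheap and removes the ambiguity; the design does not fail without it.

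**What to change.** In section 2.5, replace each count rule with a statement that an arm's null is rejected if the one-sided exact binomial p-value, computed on the number of patients actually in that arm's primary analysis set, is at most 0.05. Keep the counts only as illustrations, labelled with the planned n. Repeat the test in section 2.6 as the primary analysis. The two separate matters, the count of 12 at n = 27 and the null rate in arm C, need their own correction, because the p-value rule requires one stated null per arm.

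Optionally, report a two-sided 90% Clopper-Pearson interval alongside. Its lower limit excludes the null when the one-sided 5% test rejects; at 13/27 it is 31.3% to 65.3%.

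The cost is one sentence in each section, with no extra patients or data. The only downside is that the cut-off is no longer a single printed number.

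### Section 2.5 gives arm C two different null pCR rates, 15% for sizing and 10% in the rejection rule; the other figures fit 15%

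*Protocol article*

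**What the plan says.** Section 2.5 (Sample size) of the protocol article sets up arm C, the *BRAF* wild-type arm, in three steps.

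- Expected rate: "a pCR rate of about 30% may be assumed in arm C".
- Sizing: 34 patients give 80% power at a true rate of 35% for "rejecting a pCR rate of 15% with an exact 5% one-sided significance test".
- Decision rule: "The null hypothesis of a pCR of 10% will be rejected if a pCR is observed in at least 10 patients".

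The sizing step names a null of 15% and the decision rule names a null of 10%. The preceding paragraph, on arms A and B, is built the same way and uses one null rate, 30%, in both places. Section 2.6 (Data analysis) names no null; it says only that the primary endpoint is reported as counts and rates with confidence intervals.

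**The concern.** The decision sentence should restate the hypothesis for which the arm was sized. It names a different one. This is the only hypothesis and decision rule that the article gives for the primary endpoint in arm C, so the reader cannot tell from the text which rate a successful arm is meant to exceed.

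Two things depend on the answer. One is the published claim: exceeding 10% and exceeding 15% are different statements about activity. The other is how a result just short of the cut-off is described. Someone holding to the printed 10% null could test it directly and report a rejection with fewer than 10 pCRs, while someone holding to the printed cut-off would report none. If the conflict is settled only once the count is known, the choice will look driven by the data.

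**Working it through.** **Inputs**, all from section 2.5: n = 34; cut-off r = 10; exact one-sided test at 5%; null rate 15% (sizing) or 10% (decision rule); alternative 35%; expected rate about 30%.

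**Formula.** For X binomial(n, p), P(X ≥ r | n, p) = Σ C(n, k) p^k (1 − p)^(n − k), summed over k = r to n. Evaluated at the null rate this is the size of the rule; at the alternative it is the power.

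**Exact tail probabilities P(X ≥ r) for n = 34**

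| r | p = 0.10 | p = 0.15 | p = 0.30 | p = 0.35 |
|---|---|---|---|---|
| 6 | 0.1185 | 0.4027 | 0.9666 | 0.9923 |
| 7 | 0.0481 | 0.2409 | 0.9215 | 0.9781 |
| 8 | 0.0169 | 0.1267 | 0.8442 | 0.9473 |
| 9 | 0.0051 | 0.0587 | 0.7323 | 0.8914 |
| 10 | 0.0014 | 0.0240 | 0.5939 | 0.8045 |

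**Step 1: reproduce the plan's figures with a null of 15%.** A cut-off of 9 has size 0.0587, above 5%. A cut-off of 10 has size 0.0240. So 10 is the smallest valid cut-off, and its power at 35% is 0.8045. Sample size, power and cut-off all agree with the text.

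**Step 2: repeat with a null of 10%.** The smallest cut-off with size at most 5% is 7 (0.0481; a cut-off of 6 gives 0.1185). Its power is 0.978 at 35% and 0.922 at 30%, not 80%. The printed cut-off of 10 has size 0.0014. Against a 10% null, an exact search for the smallest n with 80% power at one-sided 5% gives 18 patients for an alternative of 35% and 25 for an alternative of 30%. Neither is close to 34.

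**Step 3: check whether another significance level changes the picture.** For 15% against 35%, the smallest n with 80% power is 28 (cut-off 8) at one-sided 5%, and exactly 34 (cut-off 10) at one-sided 2.5%. So 34 is sufficient, as the text says, though not minimal at 5%. With n = 34 and a 10% null, the 2.5% cut-off would be 8 (0.0169). At either level the cut-off of 10 belongs to 15%.

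**Step 4: find where the two nulls lead to different conclusions at one-sided 5%.**

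- 10 or more pCRs: both are rejected (p at most 0.0014 and 0.0240). For 10/34 = 29.4%, the one-sided 95% exact lower limit is 16.9%.
- 7, 8 or 9 pCRs (20.6%, 23.5%, 26.5%): 10% is rejected (p = 0.0481, 0.0169, 0.0051) and 15% is not (p = 0.2409, 0.1267, 0.0587).
- 6 or fewer: neither is rejected (p at least 0.1185 and 0.4027).

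**Step 5: probability of 7 to 9 pCRs**, as P(X ≥ 7) − P(X ≥ 10):

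- true rate 30%: 0.9215 − 0.5939 = 0.328;
- true rate 35%: 0.9781 − 0.8045 = 0.174.

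**The case against.** The strongest reply is that the decision rule is not in doubt. The cut-off appears once, as a plain count, and a cut-off of 7 appears nowhere. Taken literally, 7 to 9 pCRs fail the rule whichever null was meant, so the 33% and 17% are chances that the wording of the conclusion could be disputed, not chances that the prespecified decision reverses. This stands.

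A reader might also infer that the cut-off is invalid under 10%, or that the type I error is inflated. It is not: a size of 0.14% is very conservative, but it respects the 5% limit. Nor is it true that nobody can say what a positive arm C means. Reaching 10 of 34 rejects both rates, and even the two-sided 95% exact lower limit (15.1%) lies above 15%.

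The consequences are limited too. This is a non-comparative phase II trial, and the rate will be published with a confidence interval that readers can set against either figure. The article condenses a full protocol that is not shown, so the slip may not be present there.

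None of this removes the contradiction. Both figures are printed in adjacent sentences of the same paragraph, and the sentence that defines the test names a rate for which its own cut-off is not the 5% critical value.

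**Conclusion.** The point holds as an inconsistency in one figure. Section 2.5 states two null rates for arm C. The sample size, the power and the cut-off all fit 15%, and none of them fits 10%, so 10% is most likely the slip. That is an inference from the arithmetic, not something the document says, and only the sponsor can confirm it.

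It would go too far to conclude that the outcome of arm C is undefined. A count of 10 or more is positive against both rates, and a count of 6 or fewer is negative against both. Only the null named in the claim and the interpretation of 7 to 9 pCRs are affected. The probability of that band is 33% at the 30% that the article itself expects and 17% at the 35% used for power, assuming 34 evaluated patients and an exact one-sided 5% binomial test.

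It still needs correcting before the primary analysis, because it concerns the hypothesis for the primary endpoint and a correction made after the count is known would not be credible.

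**What to change.** The sponsor should confirm the intended null rate for arm C and state it once, before the primary analysis, in the protocol and wherever else the rule is repeated.

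- If it is 15%, as the other figures indicate: replace 10% with 15% in the rejection rule and keep 10 or more of 34. Adding the attained size (2.4%) and the power at 35% (80.4%) would help readers but is optional. The cost is one number, with no change to enrolment.
- If it is 10%: restate the sizing sentence, cut-off, size and power so that they agree. With 34 patients, the 5% exact cut-off would be 7 or more (size 4.8%, power 97.8% at 35%). If the cut-off of 10 is kept deliberately, say so and give its size of 0.14%.

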### Data analysis

2.6

All enrolled patients receiving at least one dose of the study medication will be considered the intention-to-treat population (ITT). The patient subgroup of the ITT population receiving at least one dose of the study drug will define the safety population. The analysis of efficacy endpoints will be performed in the ITT population, whereas the safety analysis will be performed in the safety population. A primary data analysis assessing the primary endpoint will be available after the neoadjuvant phase. A final data analysis will be available at study closure. The safety analysis will be completed within 12 months from the last visit of the last patient.

Primary endpoint results will be reported as counts and rates with confidence intervals. No comparisons among arms are planned. Demographical and clinical characteristics will be presented as descriptive statistics and summarized according to the treatment arm. Categorical variables will be given as counts and percentages, quantitative ones as mean and standard deviation, or median and interquartile range, as appropriate. No adjustment for multiple testing will be made.

Safety and tolerability will be assessed regarding AEs, laboratory data, ECG data, vital signs, and weight, which will be collected for all patients. AEs [both in terms of MedDRA preferred terms (26) and CTCAE 5.0 grade (27)], laboratory data, ECG data, vital signs data, and weight will be listed individually by the patient and summarized. Prevalence of related AEs, by grade, will be presented with a 95% CI. Survival will be represented with Kaplan-Meier curves, from which the median with 95% CIs will be derived.

Due to the small sample size, statistical analysis of biomarkers data will be conducted with the aim of hypothesis generation. A complete description of the data will be done. For biomarkers that might change over time due to treatment, levels before and after treatment will be compared with appropriate statistical tests based on the data type. Correlation with outcomes will be evaluated with univariate regression models. p ≤ 0.05 will be considered significant, and no adjustment is planned for multiple comparisons due to the exploratory nature of the analysis.

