### Selection of subjects

2.2

The study will enroll 88 subjects with surgically resectable *BRAF*-mutated and *BRAF* WT cutaneous melanoma. The detailed inclusion and exclusion criteria are summarized in **Table 1**.

Table 1Eligibility criteria for NEOTIM.

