### Endpoints and assessments

2.4

Endpoints are reported in **Table 2**. The primary endpoint will be the pCR, defined as residual cancer burden = 0.

**Table 2 T2:** Study endpoints.

Primary endpoint	
•To determine the pCR rate
Secondary endpoints
•Recurrence-free survival at 2 years, 3 years, and at the end of the study. Recurrence-free survival is defined as the time from randomization to recurrence event (local or distant disease development or death). •Overall survival is defined as the time from randomization to death. •Pathological overall response rate is defined as the sum of pCR, near pCRs and pathologic partial responses. •Safety: frequency of the following treatment-emergent AEs while on treatment or within 30 days after the last study treatment: All AEs, grade 3–5 AEs, serious AEs, AEs of special interest, and AEs leading to treatment discontinuation or withdrawal from the study. •To determine molecular and immunophenotypic changes in tumor and peripheral blood by evaluating several biomarkers. Since identifying new markers for immunotherapy is rapidly evolving, the definitive list of analyses remains to be determined. The following tests are suggested (differences: baseline, during the adjuvant treatment at week 6, surgical time points, and at recurrence will be compared): •Immunoscore (densities of tumor-infiltrating CD3 and CD8 cells), as well as PD-L1 expression on tumor and immune cells, evaluated by immunohistochemical analysis with an automated quantification system and a standardized assay on tumor tissue •Circulating cytokines and chemokines profiling, evaluated by Luminex technology in patient peripheral blood samples •Myeloid-derived suppressors cells and immune cell subtypes expression and lymphocyte activation, evaluated by multicolor cytofluorimetric approach in patient peripheral blood samples •Metabolomic profiling in patient peripheral blood samples, evaluated by nuclear magnetic resonance Spectrometer (600 MHz) •Tumor mutational burden by whole-exome sequencing on tumor and matched normal tissue at baseline. •Additional analysis of protein levels (i.e., CCR5), DNA mutations, and/or mRNA analysis to enable molecular classification (e.g., CMS), as well as other exploratory markers related to immunotherapy in tumor tissues

AE: Adverse event; pCR: Pathologic complete response.

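### The population labelled ITT is the treated population: it is identical to the safety set and leaves never-dosed patients out of the reported pCR rate

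*Protocol article*

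**What the plan says.** Section 2.6 of the protocol article (Data analysis) defines two populations in consecutive sentences. The first reads "All enrolled patients receiving at least one dose of the study medication will be considered the intention-to-treat population (ITT"). The second reads "The patient subgroup of the ITT population receiving at least one dose of the study drug will define the safety population". They are then given different jobs: "The analysis of efficacy endpoints will be performed in the ITT population, whereas the safety analysis will be performed in the safety population". The article defines no other analysis set, so there is no all-randomised, all-enrolled or per-protocol population.

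Section 2.4 (Endpoints and assessments) sets the primary endpoint: "The primary endpoint will be the pCR, defined as residual cancer burden = 0". Section 2.6 adds: "Primary endpoint results will be reported as counts and rates with confidence intervals". For survival, Table 2 says "Overall survival is defined as the time from randomization to death", and recurrence-free survival has the same time origin.

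Section 2.5 (Sample size) plans 27 patients in each of arms A and B and 34 in arm C. It decides by count: the null is rejected with at least 12 pCRs in arm A or B, and with at least 10 in arm C.

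**The concern.** An intention-to-treat set is fixed at randomisation or, in an arm with no alternative allocation, at enrolment. It does not depend on what happens afterwards. Here membership depends on a later event, the first dose. That has three consequences.

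- The ITT and safety sets coincide, so assigning efficacy to one and safety to the other distinguishes nothing.
- The pCR rate is reported on treated patients, while a reader who sees ITT will take the denominator to be everyone allocated. The Discussion expects the results to be set beside a pooled analysis and another neoadjuvant trial, where it matters which patients are in the denominator.
- Recurrence-free survival and overall survival start at randomisation but are analysed only in patients who reached a first dose. A patient who recurs or dies between the two points is removed although the clock has started.

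The trial is open-label, so the allocated regimen is known before the first dose and withdrawal at that point is possible. The documents do not say how often to expect it.

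**Working it through.** **The two sets.** Let E be the enrolled patients and D those with at least one dose. The article sets ITT = E ∩ D and safety = ITT ∩ D = E ∩ D ∩ D = E ∩ D. The sets are equal unless study medication and study drug mean different things, and the article gives them no different meanings.

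**The plan's own figures.** 27 + 27 + 34 = 88, which matches section 2.2: "The study will enroll 88 subjects with surgically resectable" melanoma. The enrolment target is therefore the sum of the test denominators, with no visible allowance for patients who are never dosed.

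**Direction.** Let N be the number allocated, m the number never dosed and x the number of pCRs. A never-dosed patient contributes no pCR on study treatment. The rate on the defined set is x/(N − m) and on all allocated patients x/N. Since N − m ≤ N, the first is never smaller than the second, and they are equal when m = 0.

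**Size.** The documents do not give m, so it is an assumption. L is the exact (Clopper-Pearson) one-sided 95% lower bound, the 5% quantile of Beta(x, n − x + 1). The one-sided form was chosen to match the 5% one-sided test in section 2.5. The last column is P(X ≥ x) for X ~ Binomial(n, p0). Here p0 is 30% for arms A and B, and 15% for arm C. Section 2.5 also gives 10% for arm C, which is a separate matter.

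| Arm | m | pCR / n | Rate | L | Exact p |
|---|---|---|---|---|---|
| A or B, all allocated | – | 12/27 | 44.4% | 28.0% | 0.080 |
| A or B, dosed only | 1 | 12/26 | 46.2% | 29.2% | 0.060 |
| A or B, dosed only | 2 | 12/25 | 48.0% | 30.5% | 0.044 |
| A or B, dosed only | 3 | 12/24 | 50.0% | 31.9% | 0.031 |
| C, all enrolled | – | 9/34 | 26.5% | 14.6% | 0.059 |
| C, dosed only | 1 | 9/33 | 27.3% | 15.03% | 0.0495 |
| C, dosed only | 2 | 9/32 | 28.1% | 15.5% | 0.041 |
| C, dosed only | 3 | 9/31 | 29.0% | 16.1% | 0.034 |

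These pCR counts were chosen close to the boundary of the exact test, where the denominator matters most.

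At the design rates, the expected pCR rate over all allocated patients is p1(N − m)/N. In arms A and B, for m = 1, 2, 3, this is 0.60 × 26/27 = 57.8%, 0.60 × 25/27 = 55.6% and 0.60 × 24/27 = 53.3%, against 60% on the dosed set. In arm C it is 0.35 × 33/34 = 34.0%, 0.35 × 32/34 = 32.9% and 0.35 × 31/34 = 31.9%, against 35%.

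**Effect on the stated decision rules.** The rules compare x with 12 or 10, and x does not depend on the denominator. Twelve pCRs reject with n = 25 or n = 27; nine pCRs in arm C do not reject with n = 33 or n = 34.

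**The case against.** The strongest reply is that this is mainly a naming fault. The design section says "This study is designed as a phase II randomized, non-comparative trial, with pCR as the primary endpoint", and section 2.6 plans no comparison among arms, so no randomised contrast can be biased. Arm C is the only wild-type arm, so its patients have no alternative allocation. Analysing treated patients against a fixed reference rate is a common and defensible choice in phase II. All of this stands, and it limits the severity. It does not rescue the label, the duplicated definition or the absence of an all-allocated rate.

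A reader might infer from the table that the choice of denominator flips the trial's conclusion, since the exact p-value crosses 5% between 12/27 and 12/25 and between 9/34 and 9/33. The documents do not support that. Section 2.5 decides by fixed counts, which never-dosed patients cannot change. The crossing would arise only if an exact test were rerun on the treated number, and the article does not describe doing so. Under the count rules, a smaller treated number makes false rejection less likely: P(X ≥ 12) at 30% falls from 0.080 at n = 27 to 0.044 at n = 25. The arm A/B example also leans on a separate problem, that a cut-off of 12 does not meet 5% at n = 27; 13 is needed, with a tail probability of 0.036.

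The survival point should not be pressed far either. These endpoints are secondary and are summarised by Kaplan-Meier curves without a test against a reference. No interval from randomisation to first dose is given, so the effect cannot be sized.

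Nor does the definition drop patients who were dosed but not operated on. They are already in the set, and how their pCR status is handled may be left to the full protocol or analysis plan.

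**Conclusion.** The point holds as a mislabelled and duplicated population definition. As written, the efficacy analysis is a treated-patients analysis. Its reported pCR rate and confidence interval can only be equal to or higher than those on all allocated patients, and recurrence-free and overall survival are computed in a set that does not match their time origin.

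The size rests on an assumed number never dosed. With 12 pCRs and 2 never dosed in arm A or B, the rate rises by 48.0 − 44.4 = 3.6 percentage points and the lower bound by 30.5 − 28.0 = 2.5. With 9 pCRs and 1 never dosed in arm C, the rate rises by 27.3 − 26.5 = 0.8 points and the lower bound from 14.6% to 15.03%. If every patient is dosed, there is no effect. What changes is the reported rate, its interval and any exact test rerun on the treated number; the decisions at 12 and 10 pCRs do not. Severity is minor to moderate.

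**What to change.** Define the ITT population as all randomised patients in arms A and B and all enrolled patients in arm C. Use the actual number in each arm as the denominator; do not hard-code 27, 27 and 34, because actual enrolment may differ, and add no eligibility filter in arm C, because that would bring in another exclusion after enrolment. Count never-dosed patients as not pCR. Analyse recurrence-free and overall survival in the same set, so that it matches the randomisation time origin.

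Keep the one-dose condition for the safety population, and report pCR in that set as a sensitivity analysis labelled as treated patients. If the sponsor prefers the treated set as primary, the minimum is to rename it (treated, or modified ITT) and report the all-allocated rate beside it.

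The cost is a change of wording in the protocol and analysis plan. The planned sample size does not change. The downside is that the reported pCR rate may come out slightly lower.
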